# To assess whether indoor residual spraying can provide additional protection against clinical malaria over current best practice of long-lasting insecticidal mosquito nets in The Gambia: study protocol for a two-armed cluster-randomised trial

**DOI:** 10.1186/1745-6215-12-147

**Published:** 2011-06-10

## Abstract

**Background:**

Recently, there has been mounting interest in scaling-up vector control against malaria in Africa. It needs to be determined if indoor residual spraying (IRS with DDT) will provide significant marginal protection against malaria over current best practice of long-lasting insecticidal nets (LLINs) and prompt treatment in a controlled trial, given that DDT is currently the most persistent insecticide for IRS.

**Methods:**

A 2 armed cluster-randomised controlled trial will be conducted to assess whether DDT IRS and LLINs combined provide better protection against clinical malaria in children than LLINs alone in rural Gambia. Each cluster will be a village, or a group of small adjacent villages; all clusters will receive LLINs and half will receive IRS in addition. Study children, aged 6 months to 13 years, will be enrolled from all clusters and followed for clinical malaria using passive case detection to estimate malaria incidence for 2 malaria transmission seasons in 2010 and 2011. This will be the primary endpoint. Exposure to malaria parasites will be assessed using light and exit traps followed by detection of *Anopheles gambiae *species and sporozoite infection. Study children will be surveyed at the end of each transmission season to estimate the prevalence of *Plasmodium falciparum *infection and the prevalence of anaemia.

**Discussion:**

Practical issues concerning intervention implementation, as well as the potential benefits and risks of the study, are discussed.

**Trial Registration:**

ISRCTN01738840 - Spraying And Nets Towards malaria Elimination (SANTE)

## Background

Although progress is being made [1], malaria remains one of the world's greatest childhood killers [2], consumes almost half of the clinical services in Africa (http://www.rbm.who.int), and is a substantial obstacle to social and economic development in the tropics [3,4]. We know from historical accounts that in the 1950s and 1960s malaria was controlled using indoor residual spraying (IRS) with DDT for vector control in many parts of the tropics [5]. DDT was highly effective in reducing malaria infection, but was not used widely in Africa.

Today, Roll Back Malaria is mainly concerned with reducing the burden of disease and is gathering pace. The Global Fund to fight AIDS, Tuberculosis and Malaria (http://www.theglobalfund.org) and the US President's Malaria Initiative (http://www.fightingmalaria.gov) are major players in malaria control and strategies towards elimination in Africa, supported by a myriad of smaller players. The current recommended best practice for malaria control includes the use of Artemisinin-based combination therapies and LLINs. The protective efficacy of LLINs (or insecticide treated nets, ITNs) is well known [6] and they are the cornerstone of malaria control in many African countries, including The Gambia.

Recently, there has been mounting interest in scaling-up IRS, and DDT in particular, for malaria control in Africa as IRS is a passive and a highly equitable intervention [7,8]. In 2009, 32 countries in Africa recommended IRS for malaria control and 13 of those were using DDT (http://www.who.int/malaria/world_malaria_report_2010). In The Gambia, the National Malaria Control Programme (NMCP) implemented DDT IRS over the entire country in 2009. Given this ground swell of support for DDT-based IRS it is surprising there is still a dearth of information about the effectiveness of DDT IRS in Africa; Kouznetsov's statement in 1977 is still valid; [there is a] 'lack of evidence that [IRS] schemes... are contributing to the improvement of population health in highly endemic levels of Africa' [5]. A recent Cochrane review highlighted the paucity of high-quality trials to inform decision making about the use of IRS for malaria control [9], but considered that IRS reduces malaria incidence in areas of stable transmission.

In contrast there is much stronger evidence that ITNs, and by implication LLINs, are protective with a Cochrane Review concluding that in areas of stable malaria they reduce the incidence of uncomplicated malaria in children by 50% compared to no nets [6]. There is a small body of literature suggesting that ITNs may be more protective than IRS in areas of unstable transmission, but conclude that more trials need to be carried out [9]. The only direct comparison made between ITNs and IRS with DDT that we are aware of is in China where both treatments were used separately and had a similar efficacy [10]. Thus no large-scale trials have been carried out to investigate the use of LLINs and IRS together, in comparison with LLINs alone.

Specifically it is key to determine if IRS with DDT will provide marginal protection against malaria over current best practice of LLINs and prompt treatment in a controlled trial, given that DDT is currently the most persistent insecticide for IRS [11]. Since LLINs represent 'current best practice', we propose to measure the marginal impact of IRS with DDT on malaria in communities using LLINs and having access to rapid treatment by conducting a cluster randomised intervention trial in rural villages in Upper River Region (URR), The Gambia, a country where malaria has been declining [12,13]. Here we describe the study design and the methodology used.

### Study objectives

#### Clinical

• Primary objective: To assess whether IRS with DDT plus LLINs provide added protection against clinical malaria in children compared with LLINs alone.

• Secondary objective: To assess whether IRS with DDT plus LLINs provide added protection against anaemia and/or parasite prevalence in children compared with LLINs alone.

#### Entomological

• Primary objective: To assess whether IRS with DDT plus LLINs reduces vector density inside houses when compared with LLIN alone.

## Methods/Design

### Study area and participant eligibility

The study is situated in the far east of The Gambia, in URR, extending approximately 240 to 320 km inland from the mouth of the Gambia River on the Atlantic coast, an area of open Sudan savanna. The climate consists of a single rainy season from May to October followed by a long dry season. This defines the highly seasonal malaria transmission with most malaria episodes experienced during or immediately following the rainy season. This region covers an area of 1995 km^2 ^and is bisected by the river into the north and south banks. The population of the region was 182,586 in 2003, the most recent census, with the majority living in small rural villages in houses made with mud or cement walls and thatched or metal roofs. The study's field station is based at Basse Santa Su town (UTM coordinates 13.3167N, -14.2167W) which is the only sizeable urban area.

Villages or groups of neighbouring villages, will be selected for the study that have > 110 children aged 6 months -13 years and that are ≥2 km from another study village to reduce likelihood of movement of mosquitoes from one cluster to the next. The study cohort of children, aged 6 months - 13 years old in June in Year 1, who are village residents, will be enumerated and an average of 110/cluster will be selected randomly and invited to participate in the clinical surveys and passive case detection (PCD). In order for the results from this study to be as generalizable as possible, no distinctions will be made regarding gender, ethnic group, medical condition or physical health. Children will be included providing their carers/parents give witnessed informed written consent and, in the case of older children, assent is provided. Assurance will also be sought from carers/parents that they expect that the child will remain resident in their village during the transmission season and will not be sent away for example for live stock herding or schooling. Subjects and households are free to withdraw from participating in the study at any time without giving a reason. If consent is not provided then replacement children will be randomly selected from those remaining. In year 2, overage children will leave the study and infants aged 6 to 18 months will be recruited; any other children who have left the study, for whatever reason, will be replaced.

Study subjects will be enrolled in June 2010 in Year 1. Enumeration, recruitment and survey of study subjects and application of the interventions will take place over 2 months, before the start of the transmission season. As is customary in The Gambia, sensitisation will start by discussions with community elders and then the whole study community in order to explain the nature of the study and what will be required during the interventions and investigations. We will seek verbal consent before IRS and verification of positioning of mosquito traps, and written informed consent from the parents or caregivers of all enrolled study children. During these procedures it will be made clear that people will be able to leave the study at any time.

Informed consent will be sought at the village level after sensitization meetings attended by village community leaders and health staff (community level information sheet attached). The key attendees names and roles will be documented for each village. Witnessed verbal consent will be sought from each household head, or representative, before IRS and before population, net and house surveys.

A cohort of 8,000 children will be enrolled from all the clusters to assess the impact of the intervention on malaria. In approximately 50% of clusters, equally divided between the two study arms, 6 rooms will be selected, each with a single male sleeper, to monitor the impact of the intervention on the density of malaria vectors and their infection rate with malaria. These will be randomly selected from households that have consented to join the study, stratified by housing types in the cluster. Amongst the selected households, potential rooms will be randomly selected by numbering, the numbers being placed in a hat and withdrawn blind. If the room owner does not consent or withdraws from the study or moves away, the process will be repeated.

### Design

A cluster-randomized controlled study design will be used, as IRS is a community-level intervention and the village cluster as a suitable unit for randomization. All households in all the clusters will be offered LLIN at no cost to the recipients to enable all residents to benefit from this intervention. The clusters will then be randomized into two equal groups; all households in the villages in one group will be offered IRS and those in the other group will not. It is not possible to conduct the IRS in a blinded manner since a placebo would quickly be identified by the community as non-protective. To assess whether DDT IRS and LLINs combined provide better protection against clinical malaria in children than LLINs alone, 75- 125 children aged from 6 months to 13 years old will be sampled according to cluster size enrolled into a study cohort. These children will be followed during the malaria transmission season in 2010 and 2011. Clinical malaria will be recorded by study staff using PCD in close collaboration with government health workers both at the village and health facility levels. Parasites will be detected by a rapid diagnostic test (RDT, Paracheck Pf, Orchid Biomedical Systems, Goa, India) and treatment will follow government treatment guidelines.

The study cohort will be surveyed for malaria indices (parasite prevalence, anaemia and spleen rate) at the end of both transmission seasons to generate data for the secondary endpoints and also at baseline before the year 1 transmission season. Baseline data will be used to compare the 2 groups before the interventions and end of season survey data will be used to attempt to define a *Plasmodium falciparum *parasitaemia cut-off giving optimum sensitivity and specificity for malaria cases in this setting [14].

Exposure to malaria vector mosquitoes and parasites indoors will be assessed using CDC light traps and window traps every 4 weeks from June to December and every 8 weeks from January to May in at least 6 randomly selected households in 16 village clusters in each arm of the study. This will be followed by detection of *Anopheles gambiae *species, parity status and sporozoite infection. A schematic representation of the trial is shown in Figure 1.

**Figure 1 F1:**
[figure not shown]
**Schematic of study design**.

### Randomisation

An equal number of clusters will be randomized to receive IRS, in addition to the LLINs provided to all enrolled households, and in these all households will be treated. In cluster-randomised controlled trials it is particularly important to minimize imbalance for factors known to be highly correlated with the disease outcome; in this case age and access to health facilities and location. At the village level we will stratify by presence of a primary health care centre (PHC) and geographical location by dividing the total area into four with two of equal area on each bank of the river. Stratification for PHCs will also ensure that the larger villages are evenly distributed in the experimental groups. In addition, balanced randomization will be used to ensure that children of similar ages are enrolled at the village level.

Stratified randomisation of villages to the study groups, as outlined above, will reduce the likelihood of chance imbalances between study arms but as only relatively small number of units can be randomized in such a cluster design, both groups cannot be assumed similar for all factors. Baseline data on spleen rates, parasite prevalence and anaemia will be collected on a representative sample of enrolled children in each village at the beginning of the main transmission season in 2010 to assess imbalances in malaria at village level.

Observer bias will be reduced where feasible. Blood films will be read by microscopists blinded to the identity and intervention status of the subjects. Mosquito collector bias will be reduced by using standard light traps and exit traps, which do not rely on the ability of the fieldworker to collect specimens. Trap catches will be examined by a different person to the trap collector and they will be blinded to the trap location. The processes of the interventions, both for LLINs and IRS, will be closely monitored not only for quality but also to document any bias between the villages.

### Interventions

#### a) Indoor-residual spraying

In study clusters randomized to IRS, indoor residual spraying will use a wettable powder of DDT (DDT- WP 75) manufactured to WHO specifications and supplied by Hindustan Insecticide Ltd., New Delhi, India. Indoor surfaces will receive DDT (2 g/m^2^), in May/June, at the start of the main malaria transmission season, in 2010 and 2011. DDT-WP 75, contains 500g of DDT per 670g of product and is packaged in 670g/sachets for making up to 10L with water. The sachets are clearly labelled following WHOPES guidelines (WHO/CDS/WHOPES/2003.7) and are delivered 25/heavy duty carton.

DDT will be stored to maintain efficacy and avoid environmental contamination according to WHOPES guidelines (WHO/CDS/WHOPES/2003.7) and in accordance with the Gambian National Environmental Agency's regulations. Thus the study DDT will be stored in a similar manner to DDT being used currently by the NMCP. The cartons containing individual sachets will be clearly marked with the study name (SANTE) and stored in a locked designated area in the Central Medical Stores until the week before the IRS campaign, each year, when they will be moved to a locked designated area at the Regional Store in Basse. While in the Central and Regional Stores the DDT will be under the control of the NMCP Study Investigators, who will supervise the interventions. The product will be supplied with an expiry date 2-years post-manufacture which will extend beyond June 2011.

During the week before spraying, the sensitization team will inform villages that their village has been selected for IRS, the purpose of spraying, what is required of householders and the excepted IRS date. On the day of IRS, trained spray personnel will inform householders of the spraying schedule and repeat the purpose of spraying and what is required of householders. They will then allow the household time to prepare and vacate the house. Occupants must leave houses before spraying and any rooms occupied by sick people who cannot be moved will not be sprayed. The householder should remove all household items, including water, food, cooking utensils and toys from the house. When possible furniture should be moved outside; if this is not possible, it should be moved to the middle of the room to allow easy access for spraying walls and covered. All wall hangings should be removed. When water-jars cannot be removed they should be covered. Pets and domestic animals should be tethered away from the house. Rooms will not be sprayed if people or animals are present, if household items are not correctly removed or positioned or if the walls are covered with gloss paint. Thatch ceilings also will be sprayed but not tin or hardboard ones. Data will be collected on interior wall surfaces at baseline. Householders will be allowed back into their houses after spraying and will be asked to mop any excess solution from the floors and wash the floors with water before they allow children back into the house. They are requested not to wash, paint or re-plaster sprayed walls at least until the end of the malaria transmission season.

#### b) Long-lasting insecticidal mosquito nets

LLINs distributed during this project will be Olyset Nets, Sumitomo Chemicals. These meet WHO specifications (http://www.who.int/whopes/Long_lasting_insecticidal_nets_Aug09.pdf) with permethrin at 2% w/w incorporated into polyethylene fibres giving adequate release of permethrin for up to five years. Recipients will be offered a choice between the "large" conical (1250 cm circumference, 65 cm top, 250 cm high) and the "family" rectangular (160 cm wide × 180 cm l × 150 cm h) models. Olyset nets are supplied in individual sachets labelled by the manufacturers and they will be distributed to recipients in pre-opened individual sachets in May 2010, at the beginning of the main transmission season.

Olyset LLIN will be stored at ambient temperature in locked rooms in Banjul and Basse and will be under the control of the NMCP Study Investigators. LLIN distribution will conducted in collaboration with the Regional Government bednet distributors at no cost to the recipients. In advance of distribution, the number of beds/sleeping places and the number with LLIN in excellent condition will be counted. Distribution will be at the household level to the household head or representative to achieve one LLIN per bed/sleeping place. Net use by study children will be monitored during the middle of the transmission season in 2010 and 2011. Government Roll Back Malaria information, education and communication procedures will be followed to encourage correct net use and maintenance.

### Clinical data collection and patient treatments

Passive surveillance for malaria will be maintained throughout both transmission seasons. Parents/guardians will be encouraged to take their child to the health centre or health post identified as being closest to their home at any time their child becomes unwell. The Village Health Workers (VHW) who run the health posts will use RDTs in their diagnosis of malaria and treat malaria in children who are enrolled into the study. Nurses placed in strategic health facilities will also perform a RDT in children who present directly to them who are enrolled into the study. Project field workers or nurses will visit each VHW regularly, at least once a week, to record children with malaria episodes.

The parents of any child treated for malaria at a clinical survey or during the passive surveillance will be asked to bring their child to the nearest health facility if the child does not show improvement within 48 h. When such study subjects report to a health facility government nurses will treat the child following Gambian government guidelines and inform the study nurse stationed in that facility. The study nurse will inform the study physician of the case within a minimum of delay. If such study subjects report to the VHW, he/she will advise them to report to the nearest health facility. Referred study subjects will be compensated for transport to the health facilities.

The end of transmission season survey in December 2011 will be the final study visit for all enrolled children and also the final study visit to the villages. The final survey will be similar to the baseline and end of the first transmission season survey in the previous year.

During the course of the study participants are free to receive medication from health personnel outside the study team. During the clinical surveys, iron supplementation will be given to any enrolled child with anaemia (Hb < 9 g/dL). Artemether-lumefantrine (Co-Artem) will be given to any child with a temperature of ≥37.5°C or a history of fever in the past 48 h, and *P. falciparum *parasites detected by RDT in the absence of other detectable cause of fever. The parent/carer of any child we treat for malaria will be asked to bring their child to their nearest health post or facility if the child does not make a recovery within 48 hours. Children with severe malaria will be referred to Basse Health Centre for treatment.

During the passive surveillance for malaria, parents/carers of study children will be encourage to take their child to the nearest VHW or Health Facility if the child is unwell. In both cases children with symptoms suggestive of malaria will be tested for the presence of parasites using RDTs. Treatment for other conditions will be carried out in accordance with national guidelines and/or referral to Government health facilities.

### Entomological collections

Exposure to mosquitoes will be measured by surveillance with light traps and house exit rates estimated using window traps from June to November each year. To obtain the primary entomological endpoint light traps will be used. They are routinely used in The Gambia and are unaffected by the presence of treated nets [15]. A CDC miniature light trap will be positioned close to one sleeper protected with a LLIN. Two estimates of EIR and the number of sporozoite infective bites/child/season will be calculated: one based on light traps collections and one from exit traps. Parity will also be assessed in female mosquitoes.

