#### b) Entomological

Transmission parameters in the two arms of the study will be estimated from measurements made throughout the transmission season.

Primary: The mean number of female *An. gambiae *s.l./light trap/night inside sleeping rooms.

Secondary: The entomological inoculation rate (EIR) in each study group will be estimated as the mean number of sporozoite infective bites/child/season)

Tertiary: (i) The proportion of mosquitoes exiting houses (since DDT has repellent properties), (ii) the relative abundance of different members of the *An. gambiae *complex in light trap & exit traps collected in each arm of the trial, (iii) the relative abundance of *An. gambiae s.l. *collected outdoors (iv) the parity of *An. gambiae*, to measure mean population longevity.

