#### b) Entomological

Previous studies with experimental huts indicated that DDT IRS deterred 60-70% of mosquitoes from entering houses [28]. LLINs were not associated with a deterrent effect in Gambian houses [15]. Based on a study using light traps in an adjacent study area in 2005, we expect that the mean number of female *An. gambiae s.l. *per trap will be 4.8 (with a coefficient of variation, k = 0.44). In order to demonstrate a 60% reduction in hungry indoor mosquitoes (i.e. unfed *An. gambiae*) associated with DDT IRS, with 90% power and at the 5% level of significance, we would require 8 houses in each cluster and 12 clusters in each arm of the trial over 2 years [27]. Since the number of mosquitoes rise and fall during the rainy season we propose to sample from each house 6 times each year. To allow for loss to follow-up due to people moving house during the study period we propose to include at least 8 houses in each cluster and 15 clusters in each study arm for 2 years.

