
#### Outcome 2 - malaria transmission

Differences in malaria transmission experienced in the 2 groups will be made by comparing the mean number of mosquitoes caught indoors in houses between the intervention groups. Generalised estimating equations will be used to estimate differences in numbers of indoor-resting mosquitoes, adjusting for repeated measures within clusters and possible covariates.

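### An EIR built on exit-trap catches is biased between arms, because DDT is expected to change how many mosquitoes leave houses; Outcome 2 also labels indoor density as transmission

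*Protocol article*

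**What the plan says.** All references are to the Protocol article.

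- **EIR.** Study endpoints, b) Entomological, makes EIR in each study group the secondary entomological endpoint, expressed as infective bites per child per season. Entomological collections says that two estimates will be made, "one based on light traps collections and one from exit traps". Entomological evaluations repeats this with window traps in place of exit traps. Nothing reserves the second estimate for description only.
- **Exit behaviour.** The same endpoint list has, as a tertiary endpoint, "The proportion of mosquitoes exiting houses (since DDT has repellent properties".
- **Entry.** Sample Size Rationale, b) Entomological, cites experimental-hut work in which "DDT IRS deterred 60-70% of mosquitoes from entering houses". It adds that LLINs showed no such effect in Gambian houses.
- **Primary entomological endpoint.** The objective is vector density inside houses. The endpoint is the mean number of female *An. gambiae* s.l. per light trap per night. Entomological collections assigns it to light traps, whereas Entomological evaluations names light traps and window traps together as the way to obtain it.
- **Analysis.** The Outcome 2 part of the Analytical plan opens as follows: "Differences in malaria transmission experienced in the 2 groups will be made by comparing the mean number of mosquitoes caught indoors in houses". The next sentence fits generalised estimating equations to numbers of indoor-resting mosquitoes.

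**The concern.** A between-arm comparison needs a measuring device that works the same way in both arms. The yield of an exit trap depends on how many mosquitoes leave the room, and the protocol expects DDT to alter exactly that. A mosquito repelled before it bites can still be caught on its way out and then counts towards estimated bites. If DDT raises the proportion exiting, the exit-trap EIR understates the effect of spraying; if it lowers the proportion, the effect is overstated.

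The second issue is labelling. The objective and primary endpoint are indoor density, but the analysis text calls the indoor comparison one of malaria transmission. A repellent can reduce indoor counts without an equal fall in total biting. A reader of the results could therefore take a fall in indoor density as proof of reduced transmission. The modelled quantity, indoor-resting mosquitoes, is also not what either described trap specifically samples.

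**Working it through.** **1. The plan's own entomological figure.** Inputs from Sample Size Rationale, b) Entomological:

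- effect: "In order to demonstrate a 60% reduction in hungry indoor mosquitoes", a ratio of 0.40
- control mean: "per trap will be 4.8", so the IRS mean is 4.8 × 0.40 = 1.92
- variation: "with a coefficient of variation, k = 0.44"
- error rates: "with 90% power and at the 5% level of significance" (taken as two-sided)
- stated result: 12 clusters per arm with 8 houses each, raised to 15 clusters for loss.

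The cluster formula for means is c = 1 + (1.96 + 1.2816)² × [(s₀² + s₁²)/m + k²(μ₀² + μ₁²)] / (μ₀ − μ₁)².

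The between-cluster term alone gives 1 + 10.507 × [0.1936 × (23.04 + 3.6864)] / 8.2944 = 7.55. Poisson variation within clusters at m = 8 raises this to 8.62. The stated 12 follows if the within-cluster coefficient of variation is about 0.9 to 1.0 at m = 8. The article does not give that quantity, so 12 is plausible but neither confirmed nor refuted. The point below does not depend on it.

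**2. Bias in the exit-trap EIR.** Assume an equal sporozoite rate in the two arms and equal trap efficiency for mosquitoes that exit. Then:

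exit-trap EIR ratio = entry ratio × (exit proportion under IRS / exit proportion in control)

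The entry ratio comes from the cited deterrence: 1 − 0.60 = 0.40 or 1 − 0.70 = 0.30. The documents give no exit proportions, so the second factor is assumed and shown over a range.

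| Assumed ratio of exit proportions | Reads as, true entry ratio 0.40 | Reads as, true entry ratio 0.30 |
|---|---|---|
| 1 (no change) | 0.40 | 0.30 |
| 1.5 | 0.60 | 0.45 |
| 2 | 0.80 | 0.60 |
| 2.5 | 1.00 | 0.75 |

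The effect disappears completely at 1/0.40 = 2.5 or 1/0.30 = 3.33. A ratio below 1 biases the other way: at 0.5, a true 0.40 reads as 0.40 × 0.5 = 0.20. Only a ratio of exactly 1 leaves the comparison unbiased.

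**3. Indoor density and transmission.** The planned 60% reduction equals the lower end of the cited 60-70% deterrence, so fewer entries alone could produce it. As an illustration, assume no outdoor biting in the control arm and let a fraction d of the deterred bites move outdoors. The total biting ratio is 0.40 + d × 0.60:

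- d = 0: 0.40
- d = 0.25: 0.55
- d = 0.50: 0.70
- d = 1: 1.00

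The documents give no value for d. The light-trap indoor ratio is 0.40 in every row, so indoor density alone cannot distinguish these cases.

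**The case against.** The strongest reply is that little depends on the exit-trap EIR. It is the second of two estimates of a secondary endpoint, the light-trap estimate stands beside it, and exit rates are measured and can help interpret it. The size of the bias rests on assumed values, and with no change in exiting there is none. All of this is correct and limits the weight of the point. It does not remove it: the protocol itself fixes the exit-trap estimate for a between-arm endpoint, itself expects exiting to change, and states no correction.

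Some stronger readings are tempting but not supported.

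- *Indoor light-trap catches are not comparable either.* Indoor density is the declared objective and primary entomological endpoint. Deterrence from entry is a real effect on it, not a measurement error. Light-trap EIR likewise remains a fair measure of indoor exposure, provided DDT does not alter trap efficiency. The article vouches for light traps only in the presence of treated nets.
- *The two EIR estimates will point in opposite directions.* At an entry ratio of 0.40 this needs an exit-proportion ratio above 2.5, and no figure in the document suggests one.
- *Outdoor abundance is listed as an endpoint but never collected.* The article describes no outdoor trapping, but the method for a tertiary endpoint is detail that a condensed article may leave to the full protocol.
- *Nothing guards against reading density as transmission.* Sporozoite infection, parity and parasite prevalence in children are already planned. What is wrong is the label in the analysis text, not an absence of supporting measures.

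**Conclusion.** The point holds for the exit-trap EIR and for the wording of Outcome 2. The exit-trap EIR ratio is confounded with the intervention. Under assumed exit-proportion ratios of 1 to 2.5, a true 60% reduction in entry would appear as a reduction of between 60% and none. This rests on equal sporozoite rates, equal efficiency of the exit traps for exiting mosquitoes, and exit proportions that the documents do not supply. The direction of the bias depends on whether exiting rises or falls.

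Indoor density is a legitimate endpoint but does not by itself establish reduced transmission, because the planned effect is no larger than the deterrence the protocol cites. The two sections on the source of the primary entomological endpoint also need reconciling. The clinical primary endpoint and the entomological sample size are untouched. The changes should be made, but they concern a secondary endpoint and wording, not the main conclusion of the trial.

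**What to change.** - **Study endpoints, Entomological collections and Entomological evaluations:** define the between-arm EIR from light traps only. Keep window traps for exit proportion, species and parity. If an exit-trap EIR is still calculated, show it descriptively and not as an arm comparison.
- **Entomological evaluations:** align with Entomological collections, so that the primary entomological endpoint comes from light traps.
- **Outcome 2:** retitle as indoor vector density, matching the objective and primary endpoint, and replace indoor-resting mosquitoes with light-trap catches.
- **Interpretation:** state that reduced transmission will not be concluded from indoor density alone, but read together with the sporozoite, parity and parasite-prevalence measures already planned. State the assumption that DDT does not alter light-trap efficiency.

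The cost is wording only, with no new data collection. The downside is that one EIR estimate is no longer compared between arms and the transmission claim becomes more modest.
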